### 2.4. Outcomes

The outcome measures include primary and secondary outcomes. The primary outcome measure is a change in the PANSS negative subscale from baseline to the end of the study. The secondary outcomes are a change in Brief Negative Symptom Scale (BNSS), measurement of quality of life, the capacity of building an alliance, global functioning and for the experimental group, musical communication ability from baseline to the end of the study (see Figure 1).

#### 2.4.1. Negative Symptom Measurements

As we are investigating the effect of music therapy on negative symptoms in patients with schizophrenia, we wished to evaluate this symptom domain as carefully as possible. When measuring negative symptoms, symptoms can be divided into primary and secondary negative symptoms. The primary symptoms are the core negative symptoms which are not a consequence of, for example, the side-effects of drugs, depression or a lack of social activity. As a result, we wished to have a measure of negative symptoms (PANSS and BNSS), as well as measure symptom domains which can present themselves as negative symptoms. As a result, we have chosen to measure depressive symptoms (CDSS) and medication side-effects (UKU) in addition to the scales that measure negative symptoms specifically.

The Positive and Negative Syndrome Scale (PANSS) consists of seven items for positive symptoms, seven items for negative symptoms and 16 items for the evaluation of general psychopathology. The PANSS is validated and verified and is standard in effect studies of antipsychotics [32,33]. The Structured Clinical Interview-PANSS (SCI-PANSS) is a structured interview designed to help the interviewer in getting the information needed to perform the rating. The SCI-PANSS will be used in the study [33,34,35]. Interrater reliability has been shown to be good on the full PANSS scale score, with intraclass coefficients of 0.98–0.99, with an acceptable interclass coefficient of 0.83–0.90 when using the SCI-PANSS interview [36]. Part of the PANSS rating is video recorded and kept in the data collection, as to furthermore enable analyses of interrater reliability.

The Brief Negative Symptom Scale (BNSS) consists of 6 subscales and 13 items on anhedonia, distress, asociality, avolution, blunted affect and alogia. The advantage of the scale is a separation of appetitive and consummatory anhedonia, asociality and internal experience. It has a threefold aim of examination (knowledge of behavior, of the social context and of the report of the experience of the participant concerning everyday life) [37].

#### 2.4.2. Quality of Life and Capability of Attachment Measurements

WHOQOL-Bref (Quality of Life) is a self-reported questionnaire containing 26 items. Each item is rated on a Likert-type scale ranging from zero to five, where zero is very bad and five is very good [38].

The Helping Alliance Questionnaire (Patient Version) (Haq-II) is a self-reported questionnaire containing 19 items rated on a Likert-type scale with a score from zero to six, spanning from do not agree at all to total agreement [39]. The measurement tool is important to investigate if a potential reduction of negative symptoms may increase the ability of building alliances. A former research project showed positive results in the increase of alliance building in music therapy treatment in a study population including patients diagnosed with schizophrenia [40].

#### 2.4.3. Measuring Secondary Negative Symptoms

The Calgary Depression Scale for Schizophrenia (CDSS) is used as a scale of depression for schizophrenia. Depression symptoms can be difficult to differentiate from the negative symptoms seen in schizophrenia. The CDSS consists of nine items. The CDSS is reliable and valid for the evaluation of depression in schizophrenia, and in differentiating depression from negative symptoms when combined with PANSS [41]. Each item can be given a score between 0 and 3, which gives a total score between 0 and 27. Light depression is defined as a total score ≥3 but <7, moderate depression is defined as a total score ≥7 but <11 and severe depression is defined as a total score ≥11.

UKU is an acronym for the Danish name “Udvalg for Kliniske Undersøgelser” (Task Force for Clinical Investigations). The UKU side-effects scale is used for a general assessment of side-effects induced by treatment with antipsychotics. The UKU scale is divided into four main areas: Mental, neurological, autonomic and other side-effects, containing a total of 48 items rated by the clinician [42].

#### 2.4.4. Measuring State of Functioning

The Global Assessment of Functioning (GAF) scale is a clinical evaluation of the participant’s overall function levels. Generally, it includes psychological, social, interpersonal and occupational functioning in regard to mental-health illness. The scale ranges from 0–100, with a higher number indicating superior functioning [43].

#### 2.4.5. Measurement of Musical Communication Ability

The Musical Interaction Rating Scale (MIR(S)) is applied solely for participants in group I if musical improvisation takes place in sessions 1, 15 and 25. It is a non-standardized tool specifically created for music therapy to analyze and rate musical interactions (the musical contact) between the participant and the therapist. Ten items are rated, ranging from no contact to fluent contact between the therapist and participant [44,45,46].

#### 2.4.6. Other Measurements

For each session, a detailed therapy session report is filled in. Different versions of the reports are available depending on which group the participant is randomized to. The report documents attendance, choice of techniques by the therapist, choice of music by the therapist or the participant, and finally the musical and verbal initiative of the participant.

At the four weeks follow-up, a semi-structured interview will take place, performed by the same researcher for all participants. A four-week timespan was chosen as the participants most commonly are chronically ill, and cognitive deficits could result in recall bias.

The interview is structured in two parts. The first part consists of short questions about self-experienced progressions concerning the participant’s work situation, family and social relationships and activities and personal issues (self-reliance concerning hygiene and cleaning). The second part consists of open questions about the participant’s experiences of joining the music therapy activity sessions. To create a safe setting around this interview, it is important that there is sufficient time and that it is performed where the participant wants the session to take place (e.g., at the participant’s private home, at a bench close to home, in the same room as the music therapy activities have taken place or at the place of the screening procedures).

### 2.5. Data Collection and Management

#### Case Report Form and REDCap

All data from the screening procedures will be collected in a case report form for each participant, excluding the semi-structured qualitative interview data and session schedule data. All data collected will further be entered into a REDCap electronic database, utilizing double entry to minimize the risk of errors. All information from the case report forms will be stored by the Aalborg University Hospital Psychiatry Department. When screening procedures take place on sites away from the hospital, the screening data of each case will be kept in a client project report, which is held securely until the project leader transports the data files to the hospital where they are entered into REDCap.

Data from semi-structured interviews and session schedules will be stored by The Music Therapy Clinic, an integrated institution between Aalborg University and the Aalborg University Hospital Psychiatry Department. Therapy session reports are sent by each of the therapists immediately after each session by secure mail to the coordinator, who saves the files at a secure electronic drive. Qualitative interviews are kept by the interviewer in a locked closet until the study is finished and the data have to be analyzed. These data are not entered into REDCap.

### 2.6. Ethical Approval

#### Different Approvals

This study protocol is approved by The Regional Committee on Biomedical Research Ethics, Region of Northern Jutland, Denmark (ID N-20150054) and the Data Protection Agency of Denmark (2015-144). The study is performed in accordance with the Declaration of Helsinki. Written informed consent forms will be obtained before participant inclusion in the study. A detailed signed cooperation agreement between the university and the hospital is developed for this study and a signed agreement from the heads of psychiatric centers from each community will be required before any recruitment can be initiated. The study is registered in TrialRegistration.gov (ID number NCT02942459) registered retrospectively since October 2016.

### 2.7. Sample Size

#### Estimation of Sample Size

Utilizing previous data, we estimated an effect size of 0.6 (medium effect according to Cohen’s d). With a selected level of significance of 0.05 and a power of 0.8, a power calculation performed in R with a conservative approach (applying a two-sided *t*-test with two samples), resulted in each group having to count a minimum of 44.5 persons. The data utilized in the power calculation did not use an active comparator, which might result in a lower effect size in the current study. We furthermore estimate a drop-out of 10–20% of participants, resulting in an estimated required sample size of 60 persons in each group.

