#### 1.1.3. Previous Positive Results

Three Cochrane reviews [4,6,7] have shown the positive effect of music therapy in patients diagnosed with schizophrenia, with an improvement of several general symptoms (among others, attention and motivation) and a reduction of negative symptoms. The main intervention methods of the studies have been (1) musical improvisation (where the music therapist plays a frame around the expression of the client and thus helps provide a musical structure where the client can feel like being a real part of interplay) and (2) song-writing (where the music therapist helps the client to structure texts made by the client and create a melody and musical accompaniment so they can sing the song, based on the text by the client, together. The studies were based on humanistic, resource-oriented and psychodynamic approaches. In all studies included, music therapy was added to standard care and compared to standard care alone. These reviews do not examine which elements in music therapy contribute to the overall effects observed. Qualitative research in the form of case studies has elucidated which elements in music therapy are assumed to be effective in the treatment. Musical elements, as well as elements in the therapeutic relationship seem to be crucial. Basic communication elements such as turn-taking in giving and taking a tone, a rhythm or a small melody are assumed to be effective in musical communication [12,13,14]. Additionally, joint musical expression at a very slow tempo, with as many repetitions as needed, are assumed to be effective in musical interplay [15,16]. These communication forms would not be as effective or meaningful in verbal communication. Furthermore, patients report it is meaningful to play or vocalize simultaneously with the therapist when the therapist follows the expression of the patient either in the form of imitation, matching or affective attunement [17]. These mechanisms are not so accessible in verbally mediated treatment.

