
Intervention II is carried out by non-music therapists who are familiar with the population under examination, being carefully trained in and following a manual developed for this intervention in the study. Intervention II includes solely listening to specific playlists developed by music therapists. (This intervention is similar to one of the possible intervention methods in intervention I and thus both intervention forms can be called music therapy activities). All therapists performing intervention II are trained how to apply the playlists by a music therapist. Therapists performing intervention I have, as a premise, the possibility of applying multiple music therapy techniques, including the selected playlists. Their choice of techniques is currently adapted to the needs of the participants. Both manuals are developed according to unique, essential, possible and not-possible/proscribed principles for interventions and for the attitudes of the therapist in work with this population [30,31].

All participants included in the study and clinical personal accessing the participants will be blinded. Therapists, investigators and other researchers in the research steering group, including those who make the qualitative analysis as part of the data collection, will not be blinded. The participants will be rated with the scales and measures listed below in Section 2.4.

For analyzing musical communicative capacities, only those attending intervention I will additionally be subject to audio recordings of musical improvisations in sessions 1, 15 and 25 (if improvisation is performed in those sessions), as musical improvisation is not a part of intervention II. Finally, the therapy session reports about the participants’ experiences of music listening, experiences of music performance and level of initiative in verbalization will support the results as a whole.

The study involves two regions in Denmark: The North Jutland Region and the Capital Region. Within these regions, nine municipalities are involved. A cooperation agreement is signed for each region and for each of the municipalities.

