## 3. Results

### 3.1. Statistical Analysis

#### 3.1.1. Form of Statistical Analysis

As the study is still running, no final results are available. The results will be generated through statistical analysis where the endpoints from PANSS, BNSS and WHOQOL-BREF will be analyzed using mixed model effect analysis. Predictors for the response to the treatment will be performed by multiple logistic regression, using the severity of psychiatric disorders, timespan from diagnosis identified, psychotropic medication, PANSS score results and regional contra communal treatment as usual, as explanatory variables with a regression model being performed for each of the two randomized groups. The analysis will focus on identifying predictors of improvement of negative symptoms and change of quality of life, alliance and global functioning, as well as predictors for improvement connected to treatment (music therapy activities I or II). Both per protocol and intention-to-treat analyses will be performed. Intention to treat is defined as utilizing data from all participants, even if the single participant has not attended all 25 sessions. At the time of discontinuation from the study, a final assessment will be conducted, if possible. Participants will not be followed up on after this time point.

All tests will be applied double sided and the significance limit is defined as *p* < 0.05.

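### The 80% power in section 2.7 rests on d = 0.6 from data with no active comparator, and no smaller effect is carried into the calculation for the active-listening contrast this trial tests

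*Protocol article*

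**What the plan says.** Section 2.7 sets out the calculation in a few sentences. The planning effect: "Utilizing previous data, we estimated an effect size of 0.6". The error rates: "With a selected level of significance of 0.05 and a power of 0.8". The method is described as "a power calculation performed in R with a conservative approach", which the bracket that follows explains as a two-sided, two-sample t-test. The result: "resulted in each group having to count a minimum of 44.5 persons".

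The section then qualifies its own input: "The data utilized in the power calculation did not use an active comparator". It says that this could make the effect smaller in the present trial. The next sentence adds an estimated drop-out of 10–20% and arrives at 60 per group.

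Other sections describe the two contrasts:

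- Section 1.1.3, on the Cochrane reviews: "In all studies included, music therapy was added to standard care and compared to standard care alone".
- Section 2.1, on the listening arm: "This intervention is similar to one of the possible intervention methods in intervention I". That arm receives 25 manualized sessions in the same rooms, from people who have been trained to use the playlists.
- Section 4.1 says that the design deals with the Hawthorne effect, which can favour an intervention compared only with standard care.
- Section 5 gives the current recruitment aim as 60 participants in total.

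**The concern.** A power statement belongs to one contrast. The 0.6 describes music therapy against something other than an active comparator. The trial tests music therapy against attended listening sessions that share a technique with the experimental arm. Whatever attention, contact and listening achieve by themselves is in both arms here and drops out of the difference. The protocol gives this reasoning in section 4.1 and admits the consequence in section 2.7, but the number does not change.

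The 80% is the only power figure the article gives. The trial is intended to inform Danish guideline recommendations. A reader who takes the 80% at face value would give a non-significant difference from active listening more weight than the design supports.

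**Working it through.** **Inputs from the protocol.** d = 0.6, two-sided alpha 0.05, power 0.80, 44.5 per group before and 60 per group after the drop-out allowance, and drop-out of 10–20% (all section 2.7); two-sided tests confirmed in section 3.1.1; current aim of 60 in total (section 5). Equal groups are assumed, since section 2.7 speaks of each group and gives no ratio.

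**Input assumed.** The documents give no effect against an active comparator. Suppose listening delivers a quarter to a half of the 0.6. The remaining difference is 0.6 × 0.75 = 0.45 to 0.6 × 0.5 = 0.30.

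**Step 1: reproduce the plan's figure.** The normal approximation is n = 2(1.960 + 0.842)² / 0.6² = 43.6, rounded up to 44 per group. The exact two-sample t-test (noncentral t, 2n − 2 degrees of freedom, noncentrality d√(n/2)) gives 44.59. The stated 44.5 reproduces. At n = 44.5 the noncentrality is 0.6 × √22.25 = 2.83 and the power is 79.9%.

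**Step 2: what the rounding to 60 allows for.** 44.5 / 0.9 = 49.4 and 44.5 / 0.8 = 55.6, so drop-out alone needs 50 to 56 per group. The stated 60 is 4 above the upper figure. It corresponds to drop-out of 1 − 44.5/60 = 26%.

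**Step 3: evaluable numbers.** 60 enrolled per group leaves 60 × 0.9 = 54 to 60 × 0.8 = 48. The current aim of 30 per group leaves 27 to 24.

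**Step 4: power and detectable d at those numbers** (same t-test, two-sided alpha 0.05).

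| Evaluable per group | Detectable d at 80% | Power, d = 0.6 | Power, d = 0.45 | Power, d = 0.30 |
|---|---|---|---|---|
| 54 (60 enrolled, 10% loss) | 0.54 | 87% | 64% | 34% |
| 48 (60 enrolled, 20% loss) | 0.58 | 83% | 59% | 31% |
| 44.5 (stated minimum) | 0.60 | 80% | 56% | 29% |
| 27 (30 enrolled, 10% loss) | 0.78 | 58% | 37% | 19% |
| 24 (30 enrolled, 20% loss) | 0.83 | 53% | 33% | 17% |

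Example: at n = 48 and d = 0.45 the noncentrality is 0.45 × √24 = 2.20, which gives 59%.

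**Step 5: how small a fall matters.** At d = 0.5, power is 73% with 54 and 68% with 48 evaluable per group. The planned 60 per group therefore holds 80% power only while the effect stays at or above 0.54–0.58.

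**The case against.** The strongest reply is that the protocol discloses the mismatch and its direction. That stands: nothing is concealed, and the defect is a missing adjustment.

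It can also be said that the caveat comes directly before the drop-out sentence, so 60 may have been rounded up for both reasons. The text permits that reading but states no such allowance. Step 2 shows that any allowance is small.

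The figures use the t-test of section 2.7, whereas section 3.1.1 plans a mixed model for the PANSS. Power under that model may differ, and the documents do not give what is needed to say by how much. This stands as a qualifier on every figure above.

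Three stronger readings might be inferred, and the documents do not support them:

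- *That the word conservative is wrong.* Its bracket ties it to the choice of test, not to the effect size. The two-sided test is the more demanding choice: 44.6 per group against 35.0 one-sided.
- *That a non-significant result is the likely outcome even if music therapy works.* At d = 0.45 and 60 enrolled per group, power is 59–64%, so significance is the more likely result. The statement holds at d = 0.30. At the reduced aim of 60 in total it holds for both assumed effects, but that depends on enrolment as well as on the effect size.
- *That 0.6 comes from the Cochrane comparisons with standard care alone.* Section 2.7 gives no source for its earlier data and says only that they had no active comparator. The link to section 1.1.3 is plausible but not stated.

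**Conclusion.** The point holds as a missing adjustment. Section 2.7 computes 44.5 per group correctly for d = 0.6, but by its own account that effect belongs to a comparison without an active arm. It carries no smaller effect into the number, and the rounding to 60 does not make up for this. The stated 80% is therefore not supported for music therapy against active listening.

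The size depends on an assumption. If the effect is 0.45 to 0.30, power at 60 enrolled per group is roughly 60% down to roughly 30%. At the current aim of 60 in total it is 37–33% down to 19–17%, and even at the full d = 0.6 it is only 58–53%. These figures rest on equal groups, the protocol's own 10–20% drop-out and a t-test. The detectable d (0.54–0.58 and 0.78–0.83) does not depend on the assumed effect range, so it is the firmer figure to report.

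**What to change.** In section 2.7:

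1. Label d = 0.6 as the effect against a non-active comparator.
2. Add the smallest d detectable with 80% power at the evaluable number after 10–20% drop-out, for 60 per group and for the current aim of 60 in total.
3. Add the power for the active-comparator contrast over a range of d such as 0.30–0.45, marked as an assumption, and say that it is computed for a t-test and that the planned mixed model may differ.

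The word conservative can stay, since it refers to the test.

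The cost is a few sentences and one recalculation. The stated power becomes less favourable; no extra patients are needed.

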## 3. Results

### 3.1. Statistical Analysis

#### 3.1.1. Form of Statistical Analysis

As the study is still running, no final results are available. The results will be generated through statistical analysis where the endpoints from PANSS, BNSS and WHOQOL-BREF will be analyzed using mixed model effect analysis. Predictors for the response to the treatment will be performed by multiple logistic regression, using the severity of psychiatric disorders, timespan from diagnosis identified, psychotropic medication, PANSS score results and regional contra communal treatment as usual, as explanatory variables with a regression model being performed for each of the two randomized groups. The analysis will focus on identifying predictors of improvement of negative symptoms and change of quality of life, alliance and global functioning, as well as predictors for improvement connected to treatment (music therapy activities I or II). Both per protocol and intention-to-treat analyses will be performed. Intention to treat is defined as utilizing data from all participants, even if the single participant has not attended all 25 sessions. At the time of discontinuation from the study, a final assessment will be conducted, if possible. Participants will not be followed up on after this time point.

All tests will be applied double sided and the significance limit is defined as *p* < 0.05.

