### 1.2. Hypothesis

We hypothesize that participants who are randomized to group I (the experimental group), when performed by educated and experienced music therapists offering multiple music therapy techniques adapted to the needs of the participant, will have a larger reduction in negative symptoms as measured by the clinical rating scale than participants who attend group II (the control group), where music is performed by non-music therapists, offering solely music listening. Furthermore, we hypothesize that participants randomized to group I will experience a larger increase in quality of life and in the progress of alliance building and psychosocial functioning as compared to group II.

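### The predictor analysis uses logistic regression, one model per arm, for outcomes defined as continuous changes; any responder cut-off loses at least about 36% of the information

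*Protocol article*

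**What the plan says.** Nearly all of the Protocol article works with continuous scale scores.

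- Section 2.4: "The primary outcome measure is a change in the PANSS negative subscale from baseline to the end of the study". The secondary outcomes are also framed as changes over the study.
- Section 1.2: group I "will have a larger reduction in negative symptoms as measured by the clinical rating scale".
- Section 2.7 sizes the trial with a two-sample t-test on a standardised difference of 0.6.
- Section 3.1.1: the "endpoints from PANSS, BNSS and WHOQOL-BREF will be analyzed using mixed model effect analysis".

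Section 3.1.1 then changes scale for the predictor analysis: "Predictors for the response to the treatment will be performed by multiple logistic regression". The explanatory variables are listed as "using the severity of psychiatric disorders, timespan from diagnosis identified, psychotropic medication, PANSS score results and regional contra communal treatment as usual", which makes five, "with a regression model being performed for each of the two randomized groups". The stated focus is "identifying predictors of improvement of negative symptoms and change of quality of life, alliance and global functioning".

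The article does not turn any of these scales into categories of response. The PANSS thresholds in section 2.3 are eligibility criteria, and the CDSS bands in section 2.4.3 grade depression.

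**The concern.** Logistic regression models a categorical outcome, in its ordinary form a yes/no one. To use it here, each change score must be cut into responders and non-responders. A participant just past the cut then counts the same as one who improved greatly, and two participants on either side of it count as opposites.

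This analysis can least afford that loss. Section 5 puts the current target at 60 participants in total, against 60 per group in section 2.7. The models are fitted within arm, so each has about 30 people for five predictors. Real predictors of improvement may be missed, and those reported may come from unstable fits. The results would also be on a different scale from the primary result, which concerns mean change.

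**Working it through.** **Inputs from the Protocol article.** Five explanatory variables and one model per arm (3.1.1); two-sided 0.05 (3.1.1); current target 60 in total (5), so about 30 per arm if allocation is equal; d = 0.6, power 0.8 and a stated minimum of 44.5 per group (2.7).

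**Assumptions, not in the document.** Roughly normal change scores; responder shares of 10% to 50%; a correlation of 0.35 between one predictor and the change.

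**Step 1: the plan's own figure.** A two-sided two-sample t-test with d = 0.6, alpha 0.05 and power 0.80 needs 44.59 per group. The stated 44.5 is reproduced, and it rests on a continuous outcome.

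**Step 2: information kept after a cut.** For a normal outcome with responder share p and c = z(p), the fraction kept is φ(c)² / [p(1 − p)].

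| Responder share p | φ(c) | Kept | Lost |
|---|---|---|---|
| 50% | 0.399 | 0.159 / 0.25 = 63.7% | 36% |
| 30% | 0.348 | 0.121 / 0.21 = 57.6% | 42% |
| 20% | 0.280 | 0.078 / 0.16 = 49.0% | 51% |
| 10% | 0.175 | 0.031 / 0.09 = 34.2% | 66% |

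The median split is the best case. Matching the continuous analysis there would take about 1 / 0.637 = 1.57 times as many participants.

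**Step 3: events per explanatory variable.** This is n per arm × responder share / 5.

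- At 30 per arm: 30 × 0.5 / 5 = 3.0; 30 × 0.3 / 5 = 1.8; 30 × 0.2 / 5 = 1.2.
- With 20% dropout (24 per arm): 2.4, 1.4 and 1.0.
- Even at 60 per arm the maximum is 60 × 0.5 / 5 = 6.0.

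**Step 4: simulated power for the models as written.** One arm, n = 30, five predictors, correlation 0.35 for the predictor tested. The change is cut at the median, +0.5 SD and +1 SD, giving 50%, 31% and 16% responders.

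| Analysis | 50% | 31% | 16% |
|---|---|---|---|
| Linear regression on the change (no cut) | 42-43% | 42-43% | 42-43% |
| Logistic, likelihood-ratio test | 37% | 35% | 29% |
| Logistic, Wald test | 26% | 19% | 7% |

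Linear regression holds its type I error. The likelihood-ratio test rejects in about 8-10% of null trials at the first two cut-offs, so its power there is flattered. Separation occurs in up to about a quarter of the logistic fits.

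**Step 5: a simpler model, for contrast.** With both arms pooled, N = 60, one predictor and the same correlation, linear power is about 78-79% against 61%, 57% and 46% for logistic. That is not the analysis in section 3.1.1.

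**The case against.** **The cut-off may be written elsewhere.** This is a journal article, and a responder threshold for a secondary analysis can properly sit in the full protocol or analysis plan. That stands. A reader might infer that response is left open, and that investigators, who are unblinded under section 2.1, could choose the cut after seeing the data. The document does not support this: nothing in it says who would set a cut-off or when. The point rests on the model class, which the article itself fixes.

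**Two definitions of one endpoint?** A reader might also infer that the primary outcome has been redefined. It has not. Deriving a response from a scale for a separate question leaves the outcome definition, hypothesis, sample size and mixed model untouched.

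**This is only a preference for efficiency.** Odds of response do answer a different question, and the article claims no power for this analysis. But its stated targets are improvement and change, which a continuous model addresses directly.

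**The power loss looks small in per-arm models.** With a median split and the likelihood-ratio test, a comparison at 30 per arm gave 43% linear against 39% logistic, and at 24 per arm 34% against 34%. The large gap in the pooled model therefore cannot be quoted for this plan. The near-equality is misleading, though, because the likelihood-ratio test was rejecting about 9-10% of the time under the null.

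**The text never says yes/no.** The binary outcome is inferred from the word response together with logistic regression, which is the ordinary reading. An ordinal logistic model is not excluded, but it too would need categories.

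**Conclusion.** The point holds for the predictor analysis only. Section 3.1.1 fixes a categorical-outcome model for quantities the article treats as continuous changes. Writing down a cut-off would not recover the loss: at least about 36% of the information, 42% at 30% responders and 51% at 20%, given roughly normal change scores.

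In the per-arm models with about 30 people and five predictors, a correlation of 0.35 is found with about 42-43% power by linear regression. Logistic regression manages about 26%, 19% and 7% by Wald test, or about 37%, 35% and 29% by a likelihood-ratio test whose error rate is inflated at the first two cut-offs. The correlation and responder shares are assumptions, so the exact sizes cannot be fixed from the document. Even the better analysis is underpowered: changing the model removes an avoidable loss but does not make the per-arm analysis strong.

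**What to change.** In section 3.1.1, replace multiple logistic regression with multiple linear regression, or a mixed model, on the continuous change in PANSS negative, WHOQOL-BREF and HAQ-II. Adjust for the first available value of the scale. For HAQ-II, Table 1 places that value after the fifth session. The mixed model now planned names PANSS, BNSS and WHOQOL-BREF, so the wording must be extended to cover HAQ-II. Keep any responder summary secondary or descriptive.

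Global functioning needs separate attention. Section 3.1.1 lists it as a target, but Table 1 schedules GAF only at screening and baseline, so on that schedule there is no change to model. The two places must be reconciled.

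For PANSS negative, WHOQOL-BREF and HAQ-II the cost is a wording change with no new data. The article reports recruitment still running and no final results, so as of its writing the change could precede the analysis. The downside is that results are reported as differences in mean change and not as odds ratios.
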